## 2. Materials and Methods

### 2.1. Study Design

This study adopts a quantitative, applied approach with a quasi-experimental pre–post intervention design, aimed at evaluating the feasibility and preliminary effects of a virtual reality-based intervention (exergames) on functional and perceptual outcomes in older adults at risk of frailty [23].

The intervention will be implemented in a community-based setting within the primary health care (PHC) model, in accordance with the ethical and clinical safety guidelines established by the Chilean Ministry of Health (Decree with Force of Law No. 1, 2005).

### 2.2. Study Setting and Participants

Older adults enrolled in programs aimed at maintaining comprehensive health for older populations within the primary health care (PHC) system, particularly those affiliated with the More Self-Reliant Older Adults program (+AMA) in the city of San Pedro de la Paz, Biobío Region, Chile, will be invited to participate in the implementation of this protocol. The +AMA program is a nationwide intervention implemented by municipal health departments across Chile and is designed to promote self-reliance, self-care, and active ageing among adults aged 60 years and older [24]. The groups participating in this program comprise individuals with diverse functional levels and health conditions, including both autonomous older adults and those in a pre-frail condition or at risk of frailty, thereby allowing access to a heterogeneous and representative community-based population.

The selection of +AMA program groups and other older adult groups affiliated with PHC services is based on their operational feasibility for protocol implementation. These groups are characterized by stable organizational structures and regular participant attendance, which facilitates the delivery of the intervention. Access to participants will be managed through a collaboration agreement with the Municipal Health Department (Departamento de Salud Municipal, DAS) of San Pedro de la Paz. This agreement will define the mechanisms for coordination, dissemination, and execution of the protocol within the designated community settings, ensuring appropriate collaboration between health care teams and the implementation of the planned activities.

Allocation to experimental or control conditions will be conducted at the group level, based on pre-existing community groups. This approach aims to prevent contamination between participants, preserve the natural group structure of PHC workshops, and enhance ecological validity. Given the community-based nature of the intervention, individual randomization was not feasible. Baseline comparability between groups will be examined prior to outcome analyses.

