### 2.3. Sample Size

The sample size (*n* = 40) was calculated a priori for a mixed repeated-measures design with two groups (control vs. experimental) and two assessment time points (pre- and post-intervention). The calculation assumed a significance level of α = 0.05, a statistical power (1 − β) of 0.80, and an expected small-to-moderate effect size (f = 0.25), with an assumed within-participant correlation of 0.5 and a nonsphericity correction of ε = 1.0. Under these assumptions, a minimum of 34 participants was required, evenly distributed as 17 individuals per group. Considering the potential for participant attrition and to ensure an adequate sample for pre- and post-intervention analyses, an attrition rate of approximately 15–20% was anticipated. Therefore, a total of 40 older adults will be recruited, with 20 participants allocated to the experimental group and 20 to the control group. The flow of participants through each stage of the study will be presented using a adapted CONSORT flow diagram adapted for quasi-experimental studies (Figure 1).

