#### 2.7.4. Virtual Reality-Based Falls Prevention Workshop (Intervention) (Phase 2)

##### VR-Based Program Implementation Sessions

The intervention sessions corresponding to the Virtual Reality Program for Older Adults in Primary Health Care (PHC), aimed at falls prevention, will be implemented in accordance with the guidelines established in the Information Guide for Therapeutic Interventions with Immersive Virtual Reality (INVIRTUE) [33]. The clinical objective of the program is to reduce fall risk and maintain functional capacity within the framework of strategies for preventing functional decline in older adults. The intervention will have a total duration of twelve weeks, with a frequency of two sessions per week and an approximate duration of 60 min per session. The process will be supervised by an interdisciplinary team composed of occupational therapists and speech-language pathologists, who will provide continuous clinical monitoring, personalized feedback, and timely management of any adverse symptoms associated with the use of immersive virtual reality (iVR), such as dizziness, nausea, or disorientation.

Prior to the initiation of the program, an introductory session will be conducted to familiarize participants with the technology. During this session, explanatory audiovisual content will be presented, information regarding the therapeutic objectives will be provided, and a practical demonstration of device use will be performed. Participants’ questions will be addressed, and potential concerns related to the immersive experience will be discussed.

For the deployment of the intervention, appropriate preparation of the physical environment will be essential, ensuring a spacious, safe area free of obstacles. During each session, the instructor will activate the device and establish the necessary connection to project the experience onto an external screen, allowing the remaining group members to observe the activity and participate interactively through verbal feedback.

Subsequently, each participant will directly engage with the immersive virtual reality environments under constant supervision by the professional team, ensuring safety conditions, therapeutic support, and systematic monitoring of intervention tolerance.

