### 2.8. Statistical Analysis

Data analysis will be performed using IBM SPSS Statistics software, version 30.0. Prior to analysis, data cleaning and coding procedures will be conducted to verify the absence of errors, outliers, or missing values. All statistical analyses will be carried out using a significance level of *p* < 0.05 and a 95% confidence interval.

At an initial stage, a descriptive and exploratory analysis will be conducted to characterize the sample and examine the distribution of the study variables. Sociodemographic variables (including age, sex, educational level, and comorbidities) will be summarized using absolute and relative frequencies for categorical variables, and measures of central tendency and dispersion (mean, median, standard deviation, and interquartile range) for continuous variables. Normality will be assessed using the Shapiro–Wilk test. Based on distributional assumptions, between-group comparisons will be performed using the independent-samples *t*-test for normally distributed continuous variables, the Mann–Whitney U test for ordinal variables or continuous variables with non-normal distributions, and the chi-square test for nominal variables.

To evaluate the effects of the virtual reality intervention, a two-way repeated-measures ANOVA will be conducted to test group-by-time effects (group × time). The primary analysis will follow the intention-to-treat (ITT) principle. A minimum of 20 imputed datasets will be generated, and this number may be increased depending on the proportion of incomplete data. Effect sizes will be estimated using partial eta-squared (ηp^2^) and interpreted as small (0.01), medium (0.06), or large (0.14) [36].

To control for inflation of type I error across secondary endpoints, *p* values for the prespecified secondary outcome analyses will be adjusted using the Holm–Bonferroni sequential procedure. This method was selected because it appropriately controls the family-wise error rate in the presence of multiple comparisons while being less conservative than the traditional Bonferroni correction. The correction will be applied to the secondary outcomes FES-I, ABC, SPPB, and handgrip strength. For the primary outcome, unadjusted *p* values will be reported. For the secondary outcomes, both unadjusted and Holm-adjusted *p* values will be presented, together with effect sizes and 95% confidence intervals [37].

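### Whole community groups are allocated to an arm, but the sample size and the primary ANOVA treat participants as independent; if TUG changes correlate within groups, the p values, intervals and 80% power are too optimistic

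*Protocol article*

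**What the plan says.** - **Allocation (section 2.2).** "Allocation to experimental or control conditions will be conducted at the group level, based on pre-existing community groups". The reason given is "Given the community-based nature of the intervention, individual randomization was not feasible". The section adds a check of baseline comparability between groups.
- **Sample size (section 2.3).** The calculation is for two arms and two time points, with "a significance level of α = 0.05, a statistical power (1 − β) of 0.80", f = 0.25, a within-participant correlation of 0.5 and ε = 1.0. It concludes that "a minimum of 34 participants was required, evenly distributed as 17 individuals per group", raised to 40 for attrition. It contains no ICC, design effect or number of community groups.
- **Primary analysis (section 2.8).** "a two-way repeated-measures ANOVA will be conducted to test group-by-time effects". No term for community group is named.
- **Delivery (section 2.7.4).** The VR session is projected on a screen, "allowing the remaining group members to observe the activity and participate interactively through verbal feedback". The control arm also exercises in workshops (section 2.7.6).

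**The concern.** The unit of allocation is the community group, while the unit of sizing and testing is the person. Members of a group attend the same sessions in the same setting for 12 weeks, and in the VR arm they watch and comment on each other's performance. That can make their pre-post changes resemble one another. The arm difference in mean change then carries a between-group variance component that the planned ANOVA leaves out of its error term. The standard error would be too small, and a chance difference between community groups could be declared a VR effect on TUG. The 80% power would belong to a design that the trial does not run.

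Only correlation of the *changes* matters. A stable difference in TUG level between groups is present at both visits and cancels in the group-by-time test. For the same reason, the planned baseline comparability check does not address this point.

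**Working it through.** **1. Reproduce the plan's figure.** Inputs from section 2.3: f = 0.25, ρ = 0.5, m = 2 time points, ε = 1, α = 0.05. For the group-by-time F test with independent participants:

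λ = f² × N × m / (1 − ρ), with 1 and N − 2 degrees of freedom.

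- N = 34: λ = 0.0625 × 34 × 2 / 0.5 = 8.5; df 1 and 32; power 0.807.
- N = 32: λ = 8.0; df 1 and 30; power 0.781.

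So 34 is the smallest even total that reaches 80%. It is correct, but only under independence.

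**2. Assumptions needed.** The article gives neither the ICC of the TUG change nor the number of community groups per arm (c). I take ICC 0.02, 0.05 and 0.10, equal group sizes as nearly as possible, and 17 completers per arm.

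**3. Type I error of the planned test.** With two time points the group-by-time F test equals a t test on change scores. Change was simulated with no arm effect, a between-group variance share equal to the ICC, and the unadjusted t test at nominal 5% (60,000 trials per cell):

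| Groups per arm | ICC 0.02 | ICC 0.05 | ICC 0.10 |
|---|---|---|---|
| 2 | 0.067 | 0.095 | 0.146 |
| 4 | 0.055 | 0.068 | 0.088 |
| 10 | 0.052 | 0.054 | 0.060 |
| 1 (contingency) | 0.090 | 0.151 | 0.238 |

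With the full 20 per arm the inflation is slightly larger: at ICC 0.05 it is about 0.105 with two groups per arm and 0.074 with four.

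**4. Power of a cluster-valid test.** Design effect DE = 1 + (17/c − 1) × ICC. Divide λ by DE and use 2c − 2 denominator degrees of freedom. At ICC 0.05 and 34 completers:

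| Groups per arm | DE | λ = 8.5/DE | Denominator df | Power |
|---|---|---|---|---|
| 2 | 1 + 7.5 × 0.05 = 1.375 | 6.18 | 2 | 0.30 |
| 4 | 1 + 3.25 × 0.05 = 1.163 | 7.31 | 6 | 0.62 |
| 8 | 1 + 1.125 × 0.05 = 1.056 | 8.05 | 14 | 0.75 |
| 1 | – | – | 0 | no test |

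Most of the loss comes from the degrees of freedom: even at ICC = 0 the same test has power 0.37, 0.68 and 0.77 with two, four and eight groups per arm.

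**5. Which model repairs it.** Write TUG at each visit as fixed effects plus a group intercept u, a person intercept b and error. Post minus pre removes both u and b. A random intercept for community group in a pre/post model therefore leaves the group-by-time test essentially unchanged; fitted t statistics matched those of the plain change-score test. The between-group variation in change must enter the model itself, either as a group effect on change (or on post-intervention TUG given baseline) or as a group-by-time effect.

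**The case against.** **It is a feasibility study.** Section 2.1 speaks of feasibility and preliminary effects. But H1 predicts a significant reduction compared with control, and sections 2.3 and 2.8 attach 80% power and a 5% test to it. This softens the consequence but does not remove the mismatch.

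**A separate analysis plan may deal with clustering.** The article is not silent here: it fixes both an individual-level sample size and an individual-level test. A plan that added clustering would contradict the ANOVA and void the stated power.

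**The size is assumed.** This stands. Both the ICC and the number of groups are outside the document, and with many small groups the inflation almost vanishes. Some features may also lower the ICC: tasks are tailored to each person, each participant uses the headset individually, and rotating evaluators who do not deliver the intervention assess both arms (section 3). They do not show that it is zero.

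**A stronger reading is tempting:** that each arm is one community group, so that no valid test of H1 exists. The document does not support this. Section 2.4 recruits across different groups through their representatives, and section 2.2 mentions +AMA groups and other PHC groups. That points to several groups, though it does not settle the number per arm. Nor does the article say that each group has its own staff, so that mechanism should not be assumed.

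**Conclusion.** The mismatch between allocation by group and sizing and testing by person is certain from the text. Its numerical effect is conditional on a positive ICC of TUG change and on the number of groups per arm.

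With two to four groups per arm and an ICC of 0.02 to 0.10, the nominal 5% test would run at roughly 6% to 14.5%. At ICC 0.05, cluster-valid power at 34 completers would be about 0.30 to 0.62 instead of 0.80. With about ten groups per arm the type I error is close to nominal, but with 17 to 20 people per arm that means about two people per group. Full confounding of arm and group is a contingency to be ruled out, not a finding. Because the issue bears on the validity of the primary test and the remedy is mainly wording, it should be settled before analysis.

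**What to change.** 1. State the number of community groups per arm and record group ID for every participant.
2. Replace the primary ANOVA with one of these:
   - a cluster-level comparison of group mean TUG changes;
   - a mixed model of TUG change, or of post-intervention TUG adjusted for baseline, with a random community-group effect and small-sample degrees of freedom (Kenward-Roger or Satterthwaite).
   
   If pre and post stay as repeated rows, include a random community-group-by-time effect. A random intercept for group alone is not enough.
3. Restate the power with the design effect and cluster-level degrees of freedom over a range of ICCs.
4. If there are only one or two groups per arm, report the TUG difference as an estimate and withdraw the confirmatory p value for H1.

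**Cost:** protocol and analysis wording and one data field, a less favourable power figure and wider intervals. No extra participants are needed as long as the lower power is accepted. Restoring 80% would need more: at ICC 0.05 the design effect alone gives 34 × 1.20 ≈ 41 completers with groups of 5 and 34 × 1.45 ≈ 50 with groups of 10, before the loss of degrees of freedom.

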### 2.4. Participant Recruitment

Participant recruitment will be conducted across the different groups affiliated with primary health care (PHC) services in the municipality of San Pedro de la Paz, Biobío Region, Chile.

The recruitment process will be carried out by trained research support staff. Initial contact will be made by telephone with the representatives of the participating groups, followed by the coordination of in-person visits to the locations where group activities take place. During these visits, older adults will be invited to participate in the study and will be provided with clear and comprehensible information regarding the study objectives, the general characteristics of the virtual reality (VR) intervention, its duration, and the associated assessment procedures. Emphasis will be placed on the voluntary nature of participation and on the participants’ right to withdraw from the study at any time without consequences.

Older adults who express interest in participating will be assessed to verify compliance with the established eligibility criteria. Final inclusion in the study will occur only after the informed consent form has been signed, ensuring adherence to the ethical principles of autonomy, confidentiality, and safety for older participants.

To safeguard confidentiality and anonymity, participant identification data will be coded using alphanumeric identifiers. These codes will also be used to differentiate between pre- and post-intervention measurements.

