**Figure 7 ijerph-23-00504-f007:**
[figure not shown]
A quasi-experimental Virtual Reality-Based Program for Fall Risk Reduction in Older Adults in Primary Health Care.

**Table 1 ijerph-23-00504-t001:** Inclusion and exclusion criteria.

Inclusion Criteria	Exclusion Criteria
○ Age ≥ 60 years.	○ Progressive neurological diseases or major neurocognitive disorders.
○ Functional status classified according to EFAM and the Barthel Index: autonomous older adults without risk or with mild risk of dependency.	○ Uncompensated sensory impairments.
○ Mild frailty according to Fried’s criteria or low handgrip strength (men < 27 kg; women < 16 kg).	○ Recent history of severe fractures or traumatic brain injury (TBI).
○ Timed Up and Go (TUG) test between 10 and 20 s. ○ Falls Efficacy Scale–International (FES-I) score between 20 and 40 points.	○ IMC ≥ 35.
○ Activities-specific Balance Confidence (ABC) Scale score ≥ 67%. ○ Dizziness Handicap Inventory (DHI) score ≥ 30 points. ○ Older adults who have not received interventions aimed at fall prevention or cognitive function stimulation for at least six weeks prior to study enrollment.	○ Decompensated heart disease or uncontrolled cardiac arrhythmias.
○ Provision of written informed consent.	
○ Adequate tolerance to visual and auditory stimuli.	

**Table 2 ijerph-23-00504-t002:** This is a table of Virtual Reality-Based Program for Fall Risk Reduction in Older Adults in Primary Health Care.

Activities/Exercises	Time	Description
Equipment set-up and safety check	−Pre-start to +3 min from session onset	Brief instructions, device adjustment, verification of safe area, and confirmation of participant readiness.
Warm up	5 min.	Use of exercises based on the Fall Prevention Manual for Older Adults and the Wheel within the VIVIFRAIL Program (Categories B, C1, C2, and D)
Balance 1	5 min.	Balance exercises; trunk control exercises, Weight shifting and functional reaching.
Balance 2	8 min.	Balance exercises, trunk control exercises, dynamic balance, locomotion, spatial coordination.
REST/transition	3 min.	Rest.
Balance 3	8 min.	Balance exercises, trunk control exercises, dynamic balance, locomotion, spatial coordination.
Balance 4	5 min.	Balance exercises, trunk control exercises, dynamic balance, locomotion, spatial coordination. Functional mobility.
REST/transition	3 min.	Rest.
Vestibular	8 min.	Vestibular exercises, depending on the needs of the participating older adults.
ADL	5 min.	Daily life-based exercises.

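### Intact groups are assigned to VR or conventional training without a described chance mechanism, and nothing states that the arm is withheld until consent, eligibility and baseline TUG are complete

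*Protocol article*

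**What the plan says.** Section 2.1 of the protocol article describes a "quasi-experimental pre–post intervention design". Section 2.2 sets the unit of allocation: "Allocation to experimental or control conditions will be conducted at the group level, based on pre-existing community groups". It gives three aims: "This approach aims to prevent contamination between participants, preserve the natural group structure of PHC workshops, and enhance ecological validity". The obstacle to randomisation is stated in one sentence: "Given the community-based nature of the intervention, individual randomization was not feasible". The safeguard offered in the same section is that "Baseline comparability between groups will be examined prior to outcome analyses".

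In Section 2.4, staff telephone group representatives, visit the groups and invite members. Besides the study objectives, the visit covers "the general characteristics of the virtual reality (VR) intervention, its duration, and the associated assessment procedures"; the conventional programme is not named in that list. Screening follows: "Older adults who express interest in participating will be assessed to verify compliance with the established eligibility criteria". Table 1 makes the primary outcome measure an entry criterion: "Timed Up and Go (TUG) test between 10 and 20 s".

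Section 2.7.2 allows up to two weeks for baseline assessment, then confirms eligibility, and places the introductory VR session in the third week. Section 3 provides trained evaluators who do not deliver the interventions, rotates them, and announces assessment blinding through coded identifiers and a coded time marker. The stated purpose of that coding is that pre and post measurements cannot be told apart during analysis.

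**The concern.** The reasons given support allocating whole groups. None explains why chance should not decide which whole group receives which programme. Without a lot, the choice can follow convenience or expectation, and group characteristics then become inseparable from the arm.

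The second part is the order of steps. Because allocation is by group, anyone who knows a group's arm knows it for every member. If the arm is known at the recruitment visit, the decision to volunteer can depend on it. If it is known at screening or baseline testing, so can the TUG reading, which decides entry and is also the starting value of the primary outcome. Motivation and attitude to technology, the likeliest drivers of arm-dependent volunteering, are not in the baseline battery of Section 2.7.2 or among the characteristics named in Section 2.8, so the baseline comparability check may not reveal a difference in them.

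At stake is the primary hypothesis H1, which is a comparison with the control group and not only a change within the VR group.

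**Working it through.** **1. Does the stated reason reach the decision?**

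| Reason in Section 2.2 | Argues for whole-group allocation? | Rules out a lot among whole groups? |
|---|---|---|
| Avoid contamination | yes | no |
| Keep workshop structure | yes | no |
| Ecological validity | yes | no |
| Individual randomisation not feasible | yes | no |

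**2. Is the arm hidden before baseline?** Sections 2.2, 2.4 and 2.7.2 do not say when a group's arm is fixed or announced relative to invitation, consent, screening or baseline. Section 3 describes masking of the time point at analysis. It does not mention masking of the arm when the TUG is performed.

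**3. How would a baseline shift pass through the analysis?** Section 2.8 tests group × time by repeated-measures ANOVA. With two time points this equals a two-sample comparison of change scores, so an arm-dependent shift in the baseline measurement alone enters the estimated effect in full.

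**4. Scale, from the plan's own calculation (Section 2.3).** Inputs: f = 0.25, correlation ρ = 0.5, α = 0.05, power 0.80, m = 2 time points.
- Noncentrality λ = N·m·f²/(1 − ρ). At N = 34, λ = 34 × 2 × 0.0625/0.5 = 8.5 on 1 and 32 df, giving power 0.807. At N = 32 power is 0.781. The stated minimum of 34 is reproduced.
- SD of change = SD × √(2(1 − 0.5)) = 1.0 SD.
- The planned effect is a difference in change of 4f = 1.0 SD.

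**5. Illustration (the shifts b are assumed; the article gives no TUG SD).** With n = 20 per arm and no true effect, the noncentrality of the t test is b/(1.0 × √(2/20)) on 38 df. For b = 0.3 it is 0.3/0.316 = 0.95. If the imbalance instead comes from selecting people with different TUG times, half of it is expected to regress at ρ = 0.5, so b is replaced by 0.5b.

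| Assumed b (SD) | False-positive rate, measurement shift | False-positive rate, selection imbalance |
|---|---|---|
| 0.1 | 6.1% | 5.3% |
| 0.2 | 9.5% | 6.1% |
| 0.3 | 15.2% | 7.5% |
| 0.5 | 33.8% | 12.0% |

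With 17 completers per arm, the measurement-shift column becomes 5.9%, 8.7%, 13.6% and 29.3%.

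**6. What a lot can deliver with few groups.** The number of groups and the intraclass correlation (ICC) are not given. Assume c equal groups per arm, 20 people per arm, an ICC of change of 0.01 to 0.10 and the planned 1.0 SD effect. The design effect is 1 + (20/c − 1)·ICC, tested on 2c − 2 df. Power is 0.39 to 0.27 for c = 2, 0.73 to 0.61 for c = 4 and 0.78 to 0.68 for c = 5. For c = 1 there are no df. The lot does not create this limit; it follows from allocating by group.

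**The case against.** The study is openly quasi-experimental, seeks feasibility and preliminary effects, and is meant to inform later randomised trials. Nothing is mislabelled. That stands, and it limits the point to a choice that is not justified by the reason given.

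A journal article may leave the timing and concealment of allocation to the full protocol, and Figures 1 and 7 are not shown. This also stands. A reader might infer that the arm is known at invitation, that VR groups and conventional groups hear different messages, or that staff will give VR to the most motivated group. The article says none of this. Section 2.4 can be read as one message for all groups, and no direction of bias can be taken from the text.

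Section 3 deserves credit. Evaluators are independent of delivery, rotate, are trained to a standard and follow reliability procedures. These measures reduce assessor bias, but as described they do not hide the arm at testing. It would equally be wrong to infer that evaluators do know the arm. The baseline comparability check is a further safeguard, but with 20 per arm it cannot repair selection.

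Three further inferences should be avoided:
- Section 2.9.1 defines one recruitment rate, not one per arm.
- Section 3.1 does not say how the TUG is timed.
- The 2.3 s in Section 3.1 is a measurement-error limit for an individual, not a yardstick for bias between groups.

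Finally, a lot needs groups that can host either programme, which may conflict with selecting groups for operational feasibility. That is a real cost.

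**Conclusion.** The point holds in a limited form. The protocol assigns intact groups without a described chance mechanism, on grounds that do not exclude a lot among them. It also does not state that the arm is withheld until consent, eligibility and baseline TUG are complete. Bias from choice of groups, volunteering or baseline measurement is possible, not demonstrated.

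Its size cannot be derived from the article. The false-positive rates shown rest on assumed shifts, the protocol's correlation of 0.5 and independent participants. They show that the planned test does not protect against an arm-dependent baseline measurement, not that such a shift will occur.

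The change should be made before recruitment. Withholding the arm until baseline is complete matters at least as much as the lot, because with few groups a lot gives limited balance.

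**What to change.** In Sections 2.2, 2.4 and 2.7.2:

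1. Give every participating group the same information about both programmes at the recruitment visit.
2. Complete consent, eligibility (including the TUG window) and all baseline assessments in every participating group.
3. Then assign intact groups by a lot drawn by someone outside the recruiting and assessing team.
4. Announce the arm only before the week-3 session.
5. Where a lot is impossible for a group, keep this order, withhold the arm until baseline is complete, and state the basis for its assignment.

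The cost is mainly wording and the order of steps. The two-week baseline period already precedes the week-3 session, so no extra visits or staff are needed. The downsides are that each group must be able to host either programme, the planned 20:20 split may be only approximate, and with few groups balance stays limited. The comparison should therefore still be reported as preliminary.
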